### Provisions for post-trial care {30}

None.

### Outcomes {12}

#### Primary outcomes

Primary outcomes are as follows:
The proportion of patients with relief of leukopenia and/or neutropenia.The number and proportion of patients with relief of myelosuppression-associated SAE, defined as grade 3–4 leukopenia and/or neutropenia and FN.The median and mean duration time of relief of leukopenia and/or neutropenia.The dosing of rhG-CSF.

The grading of adverse reactions is in accordance with the CTCAE 4.0.2 criteria. Leukopenia is defined as an abnormal decrease in white blood cells of less than LLN-3.0 × 10^9^/L. Neutropenia is defined as an abnormal decrease in netrophils of less than LLN-1.5 × 10^9^/L. The definition of FN is based on the IDSA guidelines (American Society of Infectious Diseases Guide 2010 edition), which is an absolute neutrophil count (ANC) of < 500 neutrophils/mcL or an anticipated decline to ≤ 500 in the next 48 h and progress to ≥ 38.3 °C orally or ≥ 38.0 °C for a duration over 1 h.

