**Methods:**

This is a randomized controlled clinical trial single-blinded for TCM decoction but not moxibustion. Patients are equally divided into the control group without decoction and moxibustion treatment (control), the decoction+moxibustion group (MD), and the placebo+moxibustion group (MP), according to the following stratification factors: age (below 40s, 40s, 50s, and 60s or above), chemotherapy regimen (anthracyclines, taxanes, anthracyclines+taxane, and others), and chemotherapy strategy (adjuvant and neoadjuvant). The TCM decoction is Wenshen Shengbai Decoction. The anticipated sample size is 462 cases (154 cases in each group). All participants are expected to treat with chemotherapy and recombinant human granulocyte colony-stimulating factor (rhG-CSF). The primary outcomes include the proportion of patients with relief of leukopenia and/or neutropenia, the myelosuppression-associated serious adverse event including grade 3–4 leukopenia and/or neutropenia, and febrile neutropenia, and the dose of rhG-CSF. The secondary outcomes include chemotherapy adherence, stratified analysis, adverse reactions, quality of life by EORTC Breast-Cancer-Specific Quality of Life Questionnaire including EORTC QLQ-C30 (V3.0) and QLQ-BR23, TCM Constitution, and 3-year disease-free survival and overall survival. Baseline information including age, surgical approach, chemotherapy regimen and strategy, pathological stage, and molecular subtype will be recorded.

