#### rhG-CSF

The rhG-CSF is performed according to the guidelines [12–14]. Patients with grade 1 myelosuppression according to the CTCAE 4.0.2 criteria are follow-up for both the intervention group and the control group. Patients with grade 2 or above myelosuppression should receive rhG-CSF treatment until the WBC count and ANC return normal. Two types of adjuvant chemotherapy regimens in breast cancer, namely ddAC-wP and TAC, can lead to a high risk of FN (incidence > 20%). According to the NCCN guidelines, prophylactic rhG-CSF treatment is recommended on day 2 or days 3 to 4 after chemotherapy. In detail, 5 mcg/kg is administrated per day until neutrophil count returns normal or nearly normal level, or long-acting rhG-CSF (PEG-rhG-CSF) is given on the second day after chemotherapy.

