### Sample size {14}

In previous studies, the incidence rate of myelosuppression was 81.0% in the control group and 61.7% in the TCM decoction group [29]. The cure rate and effective rate of the moxibustion group were 84.1% and 66.4%, while those of the control group were 35.2% and 33.3% [30]. In our preliminary study, the bone marrow suppression rate (grade 2 or above) was 52% and 81% for the MD group and the control group, respectively (δ = 15%in superiority trial). Since there are no previous data supporting the combination use of moxibustion and TCM decoction, the sample size calculation was simply based on MD/MP group versus control group, assuming that the effect of combination treatment is equivalent to or better than moxibustion or decoction alone. Considering patient enrolment at a ratio of 1:1:1 for the control, MD, and MP groups, the sample size is calculated by multiple sample rate comparisons. The sample content estimation formula is as previously described [31]. Given that *α* = 0.05 and 1-*β* = 0.08, taking a 20% drop rate into account, the required total sample size is 462 cases and 154 cases in each group.

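### Three of the four primary outcomes are worded as relief of cytopenia but the sample size rests on its incidence, so a preventive effect could be missed or reversed

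*Protocol article*

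**What the plan says.** The protocol article lists four primary outcomes (Outcomes {12}, Primary outcomes):

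1. "The proportion of patients with relief of leukopenia and/or neutropenia"
2. "The number and proportion of patients with relief of myelosuppression-associated SAE, defined as grade 3–4 leukopenia and/or neutropenia and FN"
3. "The median and mean duration time of relief of leukopenia and/or neutropenia"
4. "The dosing of rhG-CSF"

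The Methods paragraph of the abstract words the second one differently, as "the myelosuppression-associated serious adverse event including grade 3–4 leukopenia and/or neutropenia, and febrile neutropenia", with no mention of relief.

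Four other parts of the article bear on this:

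- **Entry.** Eligibility criteria {10} requires white cell and neutrophil counts before chemotherapy to exceed a normal limit (printed as the upper one). No patient enters with low counts.
- **Start of treatment.** Moxibustion begins on day 2 after chemotherapy, and the decoction is taken from day 7 of each cycle. Neither waits for cytopenia. The abstract's Background gives the aim as both prophylactic and therapeutic.
- **Background care.** All arms receive rhG-CSF. The rhG-CSF section states: "Patients with grade 2 or above myelosuppression should receive rhG-CSF treatment until the WBC count and ANC return normal". Grade 1 is only followed up.
- **Sample size {14}.** The preliminary data are that "the bone marrow suppression rate (grade 2 or above) was 52% and 81% for the MD group and the control group, respectively", with a 15-point superiority margin, and the result is 154 per group and 462 in total.

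**The concern.** Relief presupposes something to be relieved. In a trial that starts treatment before any cytopenia exists, the event that makes a patient eligible for relief occurs after randomisation, and the treatment is partly meant to prevent it. The choice of denominator then decides what is measured:

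- If only affected patients are counted, the comparison is between two post-randomisation subsets that treatment has helped to select. Prevented cases drop out of sight.
- If all randomised patients are counted, a prevented case is a patient without relief, so prevention counts against the arm that achieves it.

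For grade 2 or above, rhG-CSF until recovery is part of care in every arm, which pushes relief rates towards each other. Meanwhile the sample size was derived for a quantity on which lower is better and which is absent from the list of primary outcomes. At stake are whether outcomes 1 to 3 can show the effect the trial was sized for, and whether its stated power applies to any listed primary outcome.

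**Working it through.** **Step 1: reproduce the planned size.** Inputs from Sample size {14}: 81% and 52%, margin 15 points, α = 0.05, 20% dropout. Power is printed as 0.08 and taken here as 0.80. For superiority by a margin with unpooled variance and one-sided α = 0.05:

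n = [0.81×0.19 + 0.52×0.48] × (1.645 + 0.842)² / (0.29 − 0.15)² = 0.4035 × 6.183 / 0.0196 = 127.3, so 128 per arm.

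128 × 1.2 = 153.6, so 154 per arm; 3 × 154 = 462. This matches the printed figure exactly. A three-group arcsine comparison of the same rates does not: it gives 49 per arm, or 59 to 62 after allowing for dropout. The 462 is therefore reproduced from an incidence of grade 2 or above.

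**Step 2: what a relief proportion would show.** The incidences are the protocol's own. They are for grade 2 or above and stand in for the any-grade rates, which the article does not give. The relief rate among affected patients under this trial's background care is not given either, so it is an assumption shown over a range. Affected patients: 154 × 0.81 ≈ 125 in control and 154 × 0.52 ≈ 80 in MD. No preliminary rate is given for MP.

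*(A) Denominator all randomised, same relief rate r in both arms.* Proportion with relief = incidence × r.

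| r | Control | MD | MD − control | Chance of a significant result favouring control* |
|---|---|---|---|---|
| 100% | 81.0% | 52.0% | −29.0 | 99.9% |
| 90% | 72.9% | 46.8% | −26.1 | 99.2% |
| 80% | 64.8% | 41.6% | −23.2 | 96.5% |

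*Two-sided 0.05, 128 evaluable per arm.

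*(A′) Same denominator, unequal relief.* Even with 100% relief in MD, MD looks worse unless control relief is below 0.52/0.81 = 64.2%. Sample size {14} cites cure and effective rates from another study: 84.1% and 66.4% with moxibustion, 35.2% and 33.3% in its control group. Applied to MD and control here:

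- Cure: 0.52 × 0.841 = 43.7% against 0.81 × 0.352 = 28.5%, so MD is 15.2 points better.
- Effective: 0.52 × 0.664 = 34.5% against 0.81 × 0.333 = 27.0%, so MD is about 7.6 points better.

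*(B) Denominator affected patients only.* With equal relief the difference is zero, although 29 points of incidence separate the arms. Relief of 90% in control against 95% in MD would have about 23% power with 125 and 80 patients. With the cited cure rates the difference would be 84.1 − 35.2 = 48.9 points in favour of treatment.

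*(C) Never-affected patients counted as successes.* At 95% relief in both arms: 1 − 0.81×0.05 = 96.0% against 1 − 0.52×0.05 = 97.4%. The direction is right, but power is about 9% with 128 per arm.

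**Step 3: the same patients on the incidence endpoint.** For 81% against 52% with 128 evaluable per arm, a plain two-sided 0.05 test has 99.9% power. Against the 15-point margin, power is 80.2% at one-sided 0.05 and 70.3% at two-sided 0.05. The latter matters because the Statistical methods section prescribes two-sided tests.

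**The case against.** The other side has several good points.

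- **Therapeutic aim.** Objectives {7} speaks of treating patients who have myelosuppression, so recovery is a legitimate thing to measure. This stands: relief should be moved, not deleted.
- **The reversal depends on equal relief.** The cited cure and effective rates, put into the same formula, favour MD. This also stands, with the caveat that they come from another study of moxibustion whose background rhG-CSF the article does not describe.
- **rhG-CSF does not guarantee relief in every arm.** The instruction to treat until recovery covers grade 2 or above, whereas the outcome definitions start below the lower limit of normal and so include grade 1. Nor does it equalise the speed of recovery. Both stand.
- **Not every primary outcome is affected.** rhG-CSF dose is defined for every patient and can reflect prevention. This stands.
- **Relief may be loose wording for reduced incidence, or the full protocol may define it.** This is possible, and a missing definition in an article is not a fault in itself. But the article itself states three primary outcomes as relief, sizes the trial on incidence, and words one outcome as occurrence in the abstract and as relief in the body. If incidence was meant, the list is misworded; a duration of relief is in any case hard to read that way.

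A reader might infer that the trial's primary outcome will make an effective treatment look useless or harmful. The documents do not support that: it holds for three of four outcomes, only under particular denominators, and the apparent harm needs similar relief rates across arms.

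**Conclusion.** The concern holds in limited form. Primary outcomes 1 to 3 are conditional, in their plain sense, on a post-randomisation event that the treatment is partly meant to prevent. They do not match the endpoint behind the 462 patients, and outcome 2 conflicts with the abstract. These are contradictions in the text and need no assumption.

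The size of the damage does rest on assumptions. With equal relief of 80–100% and the grade 2 or above rates, MD looks 23–29 points worse over all randomised and no different among affected patients. With markedly lower relief in control (below 64.2% if MD reaches 100%), the all-randomised comparison favours MD. The 26-point figure at 90% relief is therefore one scenario, not a forecast. What is firm is that the direction depends on a denominator and a relief rate that the listed outcomes do not fix, and that the stated sample size was derived for none of the four.

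**What to change.** - Make the sample-size endpoint the primary outcome: the proportion of all randomised patients with at least one grade 2 or above leukopenia or neutropenia (CTCAE) during chemotherapy, taken from the weekly blood counts.
- Word the grade 3–4 and febrile neutropenia outcome as incidence over all randomised, as the abstract does.
- Keep relief, or time to recovery, as a descriptive secondary outcome for the therapeutic aim, stating that it describes affected patients only.
- Table 3 allows more than one blood test per week, so extra tests in one arm could produce extra events. Restricting the count to scheduled tests is a useful sensitivity analysis. As the main rule it would discard low counts found when a patient presents unwell between tests.

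No new data and no change to treatment are needed. The cost is a protocol and registry amendment during the trial: 218 patients were enrolled by 8 December 2019. No interim analysis is planned, and the article releases data to the analysts only after recruitment is complete, so the amendment should be dated before that release and disclosed. It will not be entirely clean, because the physicians who assess outcomes are unblinded and see individual results by arm; the report should say so.

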## Statistical methods

### Statistical methods for primary and secondary outcomes {20a}

Data were analysed using SPSS 18.0 (SPSS, lnc., Chicago, IL) and Stata10.0 (StataCorp, College Station, Texas). Multivariate analysis was performed by multiple linear regression, COX regression, or logistic regression, where appropriate. All analyses are based on two-sided test, with *P* values < 0.05 considered as statistically significant.

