#### Continuous variables

If the data shows a normal distribution, the data will be expressed as the mean ± standard deviation. Differences between groups are analysed by one-way ANOVA. If the data does not show a normal distribution, the data will be expressed as the median, lower 25% quantile, and upper 75% quantile. Differences between groups are analysed by the Kruskal-Wallis *H* test and the Nemenyi test.

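### The rhG-CSF dose, a primary outcome, has no stated scale; if it is analysed as total amount given, unadjusted body weight costs a little precision that recorded data could recover

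*Protocol article*

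**What the plan says.** - **Outcome.** Outcomes {12} names "The dosing of rhG-CSF" as a primary outcome, and the abstract's methods list "and the dose of rhG-CSF". Neither gives a unit, a weight basis or the cycles covered.
- **How rhG-CSF is given.** The rhG-CSF section has three strands:
  - The therapeutic rule carries no figure: "Patients with grade 2 or above myelosuppression should receive rhG-CSF treatment until the WBC count and ANC return normal".
  - The prophylaxis text for regimens with a high risk of febrile neutropenia gives the article's only numeric dose: "5 mcg/kg is administrated per day until neutrophil count returns normal or nearly normal level".
  - The alternative to that is "or long-acting rhG-CSF (PEG-rhG-CSF) is given on the second day after chemotherapy", with no amount and no weight basis.
- **Analysis.** For normally distributed continuous data, "Differences between groups are analysed by one-way ANOVA". Otherwise Kruskal-Wallis and Nemenyi tests apply. Section {20a} adds: "Multivariate analysis was performed by multiple linear regression, COX regression, or logistic regression, where appropriate". It lists no covariates.
- **Weight.** Table 3 ticks weight at baseline and in the every-cycle column. Weight is not a stratification factor (those are age, regimen and strategy), and nothing links it to the rhG-CSF outcome.

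**The concern.** Where a daily product is given per kg, the total received is a constant times weight times days treated. Only days carries information about marrow recovery, which moxibustion and the decoction are meant to influence. A comparison of totals that ignores weight therefore has extra variance from a known, recorded source.

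As an illustration with an assumed 7 days of treatment, 5 × 50 × 7 = 1,750 mcg for a woman of 50 kg and 5 × 75 × 7 = 2,625 mcg for one of 75 kg. That is 50% more for the same number of days. What is at stake is some power on a primary outcome. There is also the risk that, with outcome assessment not blinded to physicians, the scale is settled after the data have been seen.

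**Working it through.** **The plan's own figure.** The article states no SD, effect or power for the rhG-CSF outcome. Its 154 per group (462 in total) rests on myelosuppression rates of 81% and 52% with δ = 15%. Reading the printed power of 0.08 as 0.80 and taking a one-sided 0.05:

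(0.81×0.19 + 0.52×0.48) × (1.645 + 0.842)² / (0.29 − 0.15)² = 127.3, so 128; and 128 × 1.2 = 153.6, so 154.

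That reproduces the number but says nothing about the dose outcome, so what follows rests on assumptions.

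**Inputs.**
- From the article: 154 per group and 20% dropout, so 154 × 0.8 ≈ 123 evaluable per arm; two-sided 0.05 ("All analyses are based on two-sided test").
- Assumed: weight CV w = 0.12-0.18; CV of days among treated patients c = 0.4-0.8; weight independent of days.
- Treated share p = 0.52-0.81, borrowed from the grade 2 or above rates in Sample size {14}. It also assumes that all treated patients receive daily product per kg.

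**Variance of total dose relative to dose per kg.** With weight and treated days each scaled to mean 1:

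R = [p(1+c²)(1+w²) − p²] / [p(1+c²) − p²] = 1 + w²(1+c²)/(1+c²−p)

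- Smallest: p = 0.52, c = 0.8, w = 0.12 gives 1 + 0.0144 × 1.64/1.12 = 1.021.
- Largest: p = 0.81, c = 0.4, w = 0.18 gives 1 + 0.0324 × 1.16/0.35 = 1.107.

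**After linear adjustment for baseline weight.** The covariance of total dose with weight is p·w², so adjustment removes p²w² from the numerator. The ratio becomes R_adj = 1 + w². Adjustment recovers part of the excess, not all of it, because weight multiplies days rather than adding to them.

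**Power.** Fix the effect at 80% power for dose per kg. A mean-based test then has power Φ[(1.960 + 0.842)/√R − 1.960].

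| p | c | w | R, total | Power, total | R_adj | Power, adjusted |
|---|---|---|---|---|---|---|
| 0.52 | 0.8 | 0.12 | 1.021 | 79.2% | 1.014 | 79.4% |
| 0.52 | 0.8 | 0.15 | 1.033 | 78.7% | 1.023 | 79.1% |
| 0.52 | 0.4 | 0.18 | 1.059 | 77.7% | 1.032 | 78.7% |
| 0.81 | 0.8 | 0.15 | 1.044 | 78.3% | 1.023 | 79.1% |
| 0.81 | 0.4 | 0.15 | 1.075 | 77.1% | 1.023 | 79.1% |
| 0.81 | 0.4 | 0.18 | 1.107 | 75.9% | 1.032 | 78.7% |

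Against dose per kg, the unadjusted total loses about 1 to 4 points. Weight adjustment recovers about 2 points or less at w = 0.15 or below, and just under 3 in the extreme bottom row.

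**Simulation check.** Over 6,000 simulated two-arm trials with 123 per arm and w = 0.15, one scenario moved from 80.8% (total) to 83.1% (per kg) by t test. A rank-test example moved only from 71.6% to 72.3%.

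**Outer bound.** If every patient is treated (p = 1), R = 1 + w²(1+c²)/c². For w = 0.10-0.20 and c = 0.5-1.5 this is 1.01-1.20. It reaches 1.12-1.48 only if days barely vary (c = 0.3).

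**Chance imbalance.** At w = 0.15 the standard error of the between-arm difference in mean weight is 0.15 × √(2/123) = 1.9%, so ±3.7% is within ordinary chance.

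**The case against.** The strongest reply is that the article never says the outcome is a raw dose. Its only numeric dose is per kg, so a per-kg outcome is possible, and the unit may be settled in the full protocol or analysis plan. This stands. A reader might infer that the plan has fixed an unscaled total, but the text does not establish it, and the point is therefore conditional.

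Four further replies have force:

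- **Regression is already allowed.** Section {20a} could accommodate weight, so it cannot be said that weight will go unused. It also commits to nothing, and the group comparison actually named has no covariate.
- **Not all rhG-CSF is shown to be per kg.** The figure sits in the prophylaxis text, the therapeutic rule has none, and the long-acting product has no stated weight basis. Borrowing p from grade 2 or above rates thus mixes two settings.
- **The 50 kg and 75 kg women are individuals, not arms.** A reader might infer bias. Randomisation excludes that: chance imbalance in weight is already covered by the test's type I error.
- **Total drug used is a legitimate quantity.** The Discussion raises the expense of rhG-CSF and wants a cost-effective intervention. Replacing the total with dose per kg would change the question, so the documents do not support calling total dose wrong.

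What survives is that the scale is open in the article, and that an unadjusted total would carry avoidable variance.

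**Conclusion.** The point holds in a limited, conditional form. The primary outcome has no stated scale. If it is the total amount given, body weight adds noise wherever daily rhG-CSF is given per kg, and the named comparison does not remove it.

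Under the stated assumptions the excess variance is about 2-11%. That is worth roughly 0-2 points of power in most scenarios and up to about 4 with a mean-based test, and almost nothing with the rank test that the plan would use for non-normal data. The article supplies neither CV, and the figures also assume that weight and days are independent. Heavy use of the long-acting product could change the effect in a direction the article does not let one determine. This is a minor gain in precision and clarity; it does not threaten the validity of the comparison.

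**What to change.** 1. State the scale of the rhG-CSF outcome before analysis: the unit, the cycles covered, and how long-acting PEG-rhG-CSF is counted beside the daily product. Without that last rule, a patient's recorded dose could depend on which product she received.
2. Prespecify that the between-arm comparison of rhG-CSF dose is adjusted for baseline weight, using the multiple linear regression already allowed in {20a}. Use baseline weight as the covariate, since weights at later cycles are measured after randomisation. This keeps total drug used as the quantity compared.
3. Report dose per kg beside total micrograms, dividing each cycle's dose by that cycle's recorded weight and summing per patient.

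The cost is one covariate, one derived variable and a few sentences of definition. Weight is already collected at baseline and each cycle, and no dosing rule or patient contact changes. If the full protocol or analysis plan already defines the scale, only the adjustment needs adding.

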## Interventions

### Explanation for the choice of comparators {6b}

The control group is treated routinely without either TCM decoction or moxibustion. Both the MD and MP groups are treated with moxibustion. The MD group is additionally treated with TCM decoction, while TCM placebo is provided to the patients in the MP group.

The TCM placebo which is made of excipients and flavouring agents is used as a comparator. The packaging, shape, weight, odour, and colour of the placebo are identical to that of the Wenshen Shengbai Decoction. The placebo is manufactured by Jiangyin Tianjiang Pharmaceutical Co., Ltd., and is stored and provided to the patients by the Central Pharmacy of Yueyang Hospital.

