## Assignment of interventions: allocation

### Sequence generation {16a}

The administrative staffs are responsible for generating the random allocation sequence using SPSS and providing the treatment allocation to the physicians in sealed envelopes.

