## Assignment of interventions: blinding

### Who will be blinded {17a}

Participants in the MD and MP groups are blinded to the use of TCM. The required amount of TCM granule or TCM placebo will be provided to the corresponding participants according to the grouping each time after chemotherapy. In consideration of the patient’s safety, outcome assessments are not blinded to the physicians.

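### rhG-CSF dose, a primary outcome, depends partly on prescribing by physicians who know MD from MP, an exposure the identical placebo makes avoidable

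*Protocol article*

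**What the plan says.** **The outcome.** Outcomes {12} ends its list of primary outcomes with "The dosing of rhG-CSF". The abstract's Methods agree, closing the primary list with "and febrile neutropenia, and the dose of rhG-CSF". The article gives no unit, product, indication or period.

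**How rhG-CSF is used.** The rhG-CSF section under Interventions describes:
- Treatment: "Patients with grade 2 or above myelosuppression should receive rhG-CSF treatment until the WBC count and ANC return normal".
- Prophylaxis for two regimens at high risk of febrile neutropenia (ddAC-wP and TAC), where "prophylactic rhG-CSF treatment is recommended on day 2 or days 3 to 4 after chemotherapy". It is given either daily at 5 mcg/kg until the neutrophil count is judged normal or close to it, "or long-acting rhG-CSF (PEG-rhG-CSF) is given on the second day after chemotherapy". No rule for choosing between the products and no dose conversion is stated.

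**Who knows the arm.** Under {16a}, administrative staff generate the sequence, "providing the treatment allocation to the physicians in sealed envelopes". Under {16c}, physicians enrol patients and assign the interventions. Under {18a}, they complete the case report forms. Under {17a}, MD and MP participants are blinded to the decoction, but "outcome assessments are not blinded to the physicians", with patient safety as the reason. {17b} gives no unblinding procedure.

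**The placebo.** Under {6b}: "The packaging, shape, weight, odour, and colour of the placebo are identical to that of the Wenshen Shengbai Decoction". The Central Pharmacy of the hospital stores and supplies both. The control arm receives neither granules nor moxibustion.

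**The concern.** Most outcomes can be biased by open assessment only through how they are read or reported. With rhG-CSF dose, the physician's decision is itself the measurement. Which product is used, whether recommended prophylaxis is given, and which day a count is called recovered all change the recorded dose. Someone who expects the decoction to help could, without intending to, stop a day earlier in MD than in MP.

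MD versus MP is the only placebo-controlled contrast and the only one that isolates the decoction. The trial bears the cost of a matched placebo, yet only the patient side is masked. A difference in dose between these arms could be attributed either to the decoction or to prescribing, and the data could not separate the two.

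**Working it through.** **Plan's own figures.** The protocol gives no expected difference or standard deviation for rhG-CSF dose, so power for this outcome cannot be computed. Its sample size rests on another quantity, grade 2 or above suppression (81% control, 52% MD, margin 15 points):

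[0.81 × 0.19 + 0.52 × 0.48] × (1.645 + 0.842)² / (0.29 − 0.15)² = 127.3, rounded up to 128; 128 × 1.2 = 153.6, rounded up to 154 per arm, 462 in total.

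This reproduces the stated number if alpha is one-sided 0.05 and the printed power is read as 0.80. It says nothing about dose.

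**Where discretion enters.**

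| Step | Fixed by the protocol? |
|---|---|
| Starting treatment | Largely: CTCAE grade 2 or above, same trigger in all groups |
| Giving prophylaxis | Partly: recommended, for two regimens |
| Daily or long-acting product | No choice rule stated |
| Stopping daily prophylaxis | Partly: a judgement that the count is near enough to normal |

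**Scale of one day's discretion.** Input from the protocol: 5 mcg/kg per day, stated there for prophylaxis. Assumed: body weight 50–70 kg.
- One day: 5 × 50 = 250 mcg to 5 × 70 = 350 mcg.
- One extra day in each of four cycles (the number of ddAC cycles): 4 × 250 = 1.0 mg to 4 × 350 = 1.4 mg; at 60 kg, 1.2 mg.

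**Size relative to a course.** Assumed: the same daily dose for treatment, 3 days of treatment or 7–10 days of daily prophylaxis per cycle, 60 kg, four cycles for both.
- Treatment: 0.3 mg × 3 × 4 = 3.6 mg.
- Prophylaxis: 0.3 mg × 7 × 4 = 8.4 mg to 0.3 mg × 10 × 4 = 12 mg.
- Ratio: 8.4/3.6 = 2.3 to 12/3.6 = 3.3, whatever the weight.
- One discretionary day is 1/3 = 33% of a treatment course, and 1/10 to 1/7 = 10–14% of a prophylactic one.

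The long-acting product has no stated dose, so it cannot be placed on this scale from the documents.

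**Timing.** Granules start on day seven of each cycle, whereas prophylaxis starts on day 2 or days 3 to 4. In cycle 1, the decision to start prophylaxis and any long-acting dose precede the decoction, so an MD–MP difference in those components cannot be a decoction effect.

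**Is the exposure avoidable?** Administrative staff already hold the sequence, one pharmacy already supplies both granules, and the two products are described as matching. Nothing stated requires physicians to know MD from MP. Control and moxibustion arms cannot be masked from each other.

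**Who would benefit.** Trial status reports 218 enrolled by 8 December 2019: 462 − 218 = 244 still to be randomised at that date.

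**The case against.** The strongest reply is that prescribing is largely rule-bound. Treatment has a laboratory trigger that applies equally to all groups, and chemotherapy regimen is a stratification factor. Regimen-driven prophylaxis should therefore be roughly balanced and act mainly as noise. This stands, although the combined anthracycline–taxane stratum mixes regimens with and without recommended prophylaxis. It does not cover product choice, uptake or stopping.

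The sponsor can also say that physician unblinding is disclosed as a design choice, and that the sample size rests on MD/MP versus control, which masking cannot help. Both are true. Neither is a reason to leave the placebo contrast exposed.

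Several stronger readings are tempting, but the documents do not support them:
- *That prophylaxis is mandatory.* It is recommended.
- *That prophylactic dose cannot respond to the study treatment.* The daily product continues until counts recover, and moxibustion starts on the second day after chemotherapy, so its duration can respond.
- *That all doses are summed.* The article leaves the outcome undifferentiated; it does not state a sum.
- *That prophylaxis swamps treatment.* Four prophylactic cycles against one treatment course would give about 9 to 13 times (8.4/0.9 to 12/0.9); over equal cycles it is 2.3 to 3.3 on assumed durations.
- *That the absent unblinding procedure contradicts the safety argument.* If physicians already know the arm, no code-break is needed.
- *That one physician does everything.* The rhG-CSF section does not say who orders it; the physicians' part is inferred from {11b}, {16a} and {16c}.

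**Conclusion.** The concern holds in a limited form. A primary outcome that depends partly on discretion is measured under physicians who know MD from MP, although the matched placebo and central dispensing would allow that knowledge to be withheld. The size of any bias cannot be derived from the documents, and its presence is a risk, not a demonstrated fact. The illustration of 250–350 mcg per discretionary day rests on an assumed weight of 50–70 kg; the comparison with a course also rests on assumed durations. The conclusion further assumes that the placebo matches as described and that the treating physicians order rhG-CSF.

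The avoidable part concerns MD versus MP only. Comparisons with control are open-label whatever is done. This is a cheap improvement, not a defect that invalidates the trial.

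**What to change.** 1. **Mask MD/MP from physicians.** For patients not yet randomised, envelopes show only *control* or *moxibustion + granule kit number*. Administrative staff and the Central Pharmacy hold the key. Replace the entry in {17b} with a code-break procedure through the pharmacy, which meets the safety reason given in {17a}.
2. **Keep rhG-CSF dose as an outcome, but not on one scale.** Analyse daily and long-acting products separately, and prophylactic and therapeutic use separately.
3. **Add a supporting measure:** the number of cycles per patient in which therapeutic rhG-CSF was started after a recorded grade 2 or above count, the protocol's own trigger. It removes product and duration from the measure. It remains a decision made knowing control from moxibustion and overlaps with the incidence of suppression, so it should not replace the dose outcome.
4. **Interpretation.** Add a sensitivity analysis of MD versus MP by enrolment period (before and after masking), and report MD/MP versus control as open-label.

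None of this changes a dose or a prescribing rule. The cost is kit numbering, reprinted envelopes, a short amendment and a few added tables, with no extra staff. The main limit is that the 218 patients enrolled by December 2019, and any since, stay physician-unblinded. If recruitment has finished, item 1 and the period comparison fall away; items 2 and 3 and the open-label caveat remain possible before analysis, and MD versus MP then carries the same caveat.
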